#### School Involvement

Schools in the intervention group are offered a long-term partnership with their local EAT group, where students also deliver the EAT curriculum to Grade 7 students of the following school years. Inviting the students back is not mandatory. Students taking part in the study do not get a second intervention.

### Monitoring

#### App Stability

The stability of the Smokerface App will be monitored during the study period via the Crashlytics app (San Francisco, CA).

#### External Data Monitoring Committee

As suggested by the Standard Protocol Items: Recommendations for Interventional Trials guidelines, all primary analyses will be performed externally and the raw datasets will be sent to the Collaboration Center for Clinical Trials in Marburg, Germany, for external monitoring [54].

### Participants

Students from Germany attending Grade 7 in all types of regular secondary schools in Germany were eligible. Schools of other types such as special schools for mentally handicapped children or Rudolf Steiner schools, schools in other countries, or schools that had previously participated in an EAT event were not eligible. Schools were contacted by each study center individually, and therefore, only schools in the vicinity of the participating medical schools could enter the study.

### Procedure

Data at baseline and follow-up are collected via a published questionnaire developed for and used in our previous investigation in the same age group [53]. All items were based on three established studies declared as high quality by the recent Cochrane review [20] and were either used in their original form or adapted to the specific circumstances of the recent study [55-57]. Data for process evaluation was collected via a newly devised questionnaire asking for feedback on the curriculum, the medical students, and the Smokerface app specifically. Most items were assessed using a 4-point Likert scale.

### Data Collection

Teachers will collect the data and hand out a modified protocol, used in the Hutchinson Smoking Prevention Project, which was provided by and discussed with the authors as well as used in our previous investigation [55].

### Randomization

Schools were externally and centrally randomly allocated to the control or intervention group by the KKS in Marburg, Germany. This center used permuted-block randomization via a computer with random block sizes. Stratification by a predefined smoking prevalence (≥2.65% or <2.65%) at baseline was used to balance group allocation. Schools were allocated to the control or intervention group in a ratio of 1:1 (except for Bonn, 2:1). A total of 72 schools were randomized into the control group and intervention group.

### Outcomes

The primary outcome is the between-group difference of the change in smoking prevalence from baseline to the 24-month follow-up. Secondary outcomes are between-group differences in change in smoking-related attitudes in accordance with the theory of planned behavior and the number of new smokers, quitters, and never-smokers after 24 months. For all outcomes, the number needed to treat will be calculated. Considering the short nature of the intervention, we predefined a number needed to treat below 50 as clinically relevant. Students are defined as smokers if they report having used cigarettes, at least one day in the 30 days preceding the survey, in accordance with the established National Youth Tobacco Survey definition [58]. Students who report not having smoked cigarettes in the past 30 days were defined as nonsmokers. All participants who report having smoked more than a puff in the past (beyond the past 30 days) were defined as ex-smokers.

### Statistical Considerations

#### Sample Size Calculation

The sample size for the primary outcome was calculated with a two-sided Chi-square test and multiplied by the correction factor design effect (design effect=1 + [cluster size−1]* intraclass correlation coefficient) to adjust for correlation with regard to smoking prevalence within a cluster. We calculated an intraclass correlation coefficient of 0.033, based on the data from our recently published study on smoking behavior in Germany (analysis of variance estimator by Zou and Donner) [11,59].

To detect a between-group difference of 3% change in smoking prevalence from baseline to 24 months of follow-up with an alpha of 5% and a test power of 70%, we calculated a sample size of 5645 to 15,715 participants, depending on the difference in smoking prevalence between the two groups (2% vs 5% up to 9% vs 12%, respectively) and with an assumed dropout rate of 30% during the follow-up. Assuming an average cluster size of 100 participants, approximately 56-157 schools needed to be randomized. The dropout rate of 30% is appropriate for our 24 months of follow-up, as we observed less than 20% dropout in our recent 6-month investigations [10,11].

#### Data Entry

Data entry will be performed using the current software version of Formic Fusion by the Xerox AG (Kloten, Switzerland) and recommended scanners provided by the Interdisciplinary Centre for Educational Research at the University of Duisburg-Essen.

#### Analysis

To examine baseline differences in students’ characteristics in our experimental design, we will use Chi-square tests for the categorical variables and *t* tests for the continuous variables. To test for differences in baseline and follow-up smoking prevalence between groups, we will use a cluster-adjusted Mantel-Haenszel Chi-square test [60] at a two-sided significance level of 5%. In the main analysis, hierarchical linear models (HLM) will be applied. HLM can handle the nested structure of the data and will be used to test for between-group differences in within-group changes in smoking behavior over time. HLM will also be used to investigate the influence of further covariates (such as gender, cultural background, and social characteristics) and time-dependent behavior in secondary analyses. Statistical analyses will be performed using the newest version of SPSS Statistics (IBM Corp, Armonk, New York).

The potential effects of missing data on the results will be assessed via sensitivity analysis. For this, dropouts (ie, participants who withdraw consent for continued follow-up or who are missing in the classroom during the survey) will be included in the analysis by applying multiple imputations [61]. 

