### Trial Design

A randomized controlled multicentered trial with two parallel groups is underway (ClinicalTrials.gov: NCT02697409). A total of 13 German EAT groups are participating, each functioning as a study center. The primary outcome is the between-group difference in smoking prevalence from baseline to follow-up. Randomization was externally and centrally performed via a computer on a school level with a 1:1 allocation.

A total of 144 secondary schools in five federal states of Germany participated in the baseline survey in the first half of the school year (September 2016 to April 2017, depending on the federal state) prior to randomization. The randomization of schools based on the baseline data was performed from November 2016 through May 2017 by the Coordination Center for Clinical Studies Marburg (KKS Marburg) as a blocked randomization combined with stratified randomization by study center and smoking prevalence, in order to ensure a balance of participant characteristics in each group. Immediately after randomization, schools were informed of their group allocation (intervention or control) and appointments were made for the implementation of the EAT curriculum in the intervention group. To assess the quality of the intervention, we implemented a process evaluation including four points of view: medical student volunteers and training supervisors after training via the EAT curriculum as well as teachers and students within 24 hours postintervention. The first follow-up survey was conducted 9 months after the intervention. The second follow-up was conducted at 16 months (April 2018 to February 2019), and the third follow-up will be conducted at 2 years (December 2018 to October 2019). In order to assure comparability between the two groups, we calculated the average number of days between randomization and intervention in each study center for the intervention group and added these numbers to the randomization date of the schools in the control group when assessing the dates for the follow-up surveys.

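### The main model does not name the centre and baseline-prevalence strata used to randomise schools; adding them is a cheap gain in precision, and the 1:1 and 2:1 statements need reconciling

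*Protocol article*

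**What the plan says.** Trial Design describes "blocked randomization combined with stratified randomization by study center and smoking prevalence", with 13 centres. It also states: "Randomization was externally and centrally performed via a computer on a school level with a 1:1 allocation".

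Randomization gives the prevalence cut (2.65%), does not repeat centre as a stratification factor, and adds an exception: "Schools were allocated to the control or intervention group in a ratio of 1:1 (except for Bonn, 2:1". It does not say which arm gets the 2.

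On the main analysis, the Analysis section says: "In the main analysis, hierarchical linear models (HLM) will be applied. HLM can handle the nested structure of the data". The model tests arm differences in change over time. Additional covariates, with gender, cultural background and social characteristics as examples, go to secondary analyses. A cluster-adjusted Mantel-Haenszel test compares prevalence at baseline and follow-up. Neither centre nor prevalence stratum is mentioned for either method.

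**The concern.** Stratified randomisation removes differences between strata from the arm contrast. If the analysis does not also account for the strata, that variation stays in the error term. The reported standard error is then larger than the true sampling variation, the nominal 5% test runs below 5%, and power is lost.

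The primary outcome is change, so what counts is whether change in smoking differs by centre or stratum. A school or centre random intercept absorbs differences in level, not in change. Separately, a different ratio in one centre makes allocation depend on centre, so an analysis without centre lets part of that centre's trend into the treatment contrast.

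**Working it through.** **The plan's own sample size.** Inputs from Sample Size Calculation: "The sample size for the primary outcome was calculated with a two-sided Chi-square test and multiplied by the correction factor design effect"; prevalences "2% vs 5% up to 9% vs 12%, respectively"; "We calculated an intraclass correlation coefficient of 0.033"; cluster size 100; 30% dropout; two-sided 5%; power 70%.

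n per arm = [1.960·√(2p̄q̄) + 0.524·√(p₁q₁ + p₂q₂)]² / 0.03²

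- 2% vs 5%: 463 per arm. 9% vs 12%: 1289 per arm.
- Design effect = 1 + 99 × 0.033 = 4.267.
- 2 × 463 × 4.267 / 0.70 = 5644.6, rounded up to 5645.
- 2 × 1289 × 4.267 / 0.70 = 15,714.8, rounded up to 15,715.

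Both ends of the stated range reproduce, so the sample size is not in question.

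**Effect on the standard error.** Analysed students per school: 11,286 / 144 = 78, and 78 × 0.70 = about 55. Assume a 24-month prevalence of 9%.

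- Between-school variance: 0.033 × 0.09 × 0.91 = 0.00270.
- Within-school part: 0.0819 × 0.967 / 54.6 = 0.00145.
- Total: 0.00415.

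If centre and stratum together carry a share f of the between-school part, the large-sample ratio of unadjusted to adjusted standard error is √[0.00415 / ((1 − f) × 0.00270 + 0.00145)]. This gives 1.07, 1.16 and 1.28 for f = 20%, 40% and 60%. A simulation (144 schools, 13 centres, intervention schools per centre from Table 3, control schools per centre assumed, 3000 trials per setting) agrees, after the small cost of estimating the extra terms:

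| Assumed f | SE ratio, unadjusted/adjusted | Type I, unadjusted | Type I, adjusted |
|---|---|---|---|
| 0% | 0.99 | 4.8% | 4.7% |
| 20% | 1.06 | 3.6% | 4.2% |
| 40% | 1.15 | 2.8% | 4.8% |
| 60% | 1.26 | 1.8% | 4.7% |

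**Effect on power.** A second simulation (4000 trials per setting) used a mean prevalence of 10.5%, a true difference of 3 points, and 55 students in each of 144 schools:

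| Assumed f | Power, unadjusted | Power, adjusted |
|---|---|---|
| 0% | 74.1% | 73.3% |
| 20% | 75.0% | 78.2% |
| 40% | 77.0% | 84.7% |
| 60% | 77.8% | 90.4% |

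Its unadjusted type I error was 5.3%, 3.5%, 2.6% and 2.0%, in line with the first table.

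**The 2:1 centre.** Table 3 lists 6 of the 72 intervention schools for Bonn. A 2:1 ratio then implies 3 control schools if intervention has the larger share, or 12 if control has. The share of an arm differs by 6/72 − 3/72 = +0.042 or 6/72 − 12/72 = −0.083. The bias is that difference times the gap in change between Bonn and the other centres. For an assumed 4-point gap it is 0.17 or 0.33 points in absolute size, which is 6% or 11% of the 3-point target. In the simulation at 9% prevalence the unadjusted standard error is about 1.07 points, so the bias is about 0.16 or 0.31 standard errors.

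**The case against.** The strongest reply is that silence is not exclusion. The article lists no levels or fixed effects for the model. The nesting it mentions could include centre, and calling the later covariates additional ones leaves room for terms already in the main model. Stratification terms are often left to an analysis plan, and none is shown. This stands: a reader might infer that the main analysis leaves both factors out, but the text shows only that it does not name them. It does not settle the matter, because a prevalence stratum is not a level of nesting, and a centre intercept would not capture centre differences in change.

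The harm is also limited. The test errs on the conservative side, and unadjusted power in the simulations is 74% to 78%, above the planned 70%. The variance share is assumed. Both simulations use a single follow-up prevalence rather than change, and a change model already uses each school's baseline smoking. Control schools per centre are not reported. All of this stands, and it makes the size conditional. It does not remove the case for adjusting, since the loss if the strata carry nothing is about 1 point of power.

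**Conclusion.** The point holds as an inexpensive improvement, not as a demonstrated error. The randomisation used centre and prevalence strata, and the analysis as described names neither. If the strata predict the outcome, the unadjusted standard error is about 6% to 26% wider than it need be and type I error is about 2% to 3.6%. This rests on an assumed 20% to 60% share of between-school variance, an ICC of 0.033, and follow-up prevalence standing in for change. At a share of zero the effect vanishes.

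Two stronger inferences are not supported. That the standard error is too wide cannot be stated as fact, because the article gives no figure for how predictive the strata are. That the treatment effect is materially confounded with centre does not follow either: one centre of 13 is involved, the direction of its ratio and its control count are unstated, and the possible bias is about 0.2 to 0.3 points for an assumed 4-point gap.

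The mismatch between an unqualified 1:1 in Trial Design and a 2:1 exception in Randomization is in the text and needs correcting regardless.

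**What to change.** - In Analysis, state that the main model includes study centre and baseline-prevalence stratum. If change over time is modelled, enter them as centre-by-time and stratum-by-time terms, since main effects alone do not act on the contrast in change.
- Stratify or adjust the Mantel-Haenszel test by the same factors. Crossing them gives 13 × 2 = 26 cells, or 144 / 26 = about 5.5 schools each, so say how sparse cells are handled.
- Reconcile Trial Design with Randomization: 1:1 except one centre at 2:1, with the direction given and both stratification factors named in both places.

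The cost is a sentence or two in Analysis and one correction to the allocation text, with no new data. The terms use 12 + 1 = 13 of about 142 school-level degrees of freedom, and about 1 point of power is lost if the strata turn out not to predict the outcome. Fixing this before the 24-month analysis also avoids a later choice about adjustment.

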	6-9 days, n (%), average number of cigarettes per day		19 (0.2), 2.45	13 (0.2), 2.27	6 (0.1), 2.83
	10-19 days, n (%), average number of cigarettes per day		26 (0.2), 3.33	11 (0.2), 5.18	15 (0.3), 1.97
	20-29 days, n (%), average number of cigarettes per day		10 (0.1), 3.90	5 (0.1), 2.50	5 (0.1), 5.30
	All 30 days, n (%), average number of cigarettes per day		43 (0.4), 10.12	23 (0.4), 8.52	20 (0.4), 11.95
	Not smoked in the past 30 days (nonsmokers), n (%)		10,842 (97.4)	5532 (97.6)	5310 (97.3)
	Never tried smoking, not even a puff, n (%)		9458/11,074^a^ (85.4%)	4835 (85.7)	4623 (85.1)
	Never smoked a cigarette (never-smokers), n (%)		9296/11,002^a^ (84.5%)	4754 (85.0)	4542 (84.0)
**Ex-smokers who smoked... n (%)**					
	More than once per week		122 (1.1%)	57 (1.0%)	65 (1.2%)
	Less than once per week		122 (1.1%)	66 (1.2%)	56 (1.0%)

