**Smoking in a social environment, n (%)**					
	I have at least one smoking parent		4278 (38.5)	2188 (38.6)	2090 (38.4)
	One of my best friends smokes		1174 (11.2)	567 (10.6)	607 (11.8)
	I have an older sibling that smokes		1252 (11.7)	623 (11.5)	629 (12.0)

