### Baseline Characteristics

Our baseline survey includes the major predictors of adolescent smoking, as described in the literature [56,57]. The distributions of relevant characteristics over the two groups are balanced, indicating successful randomization. For example, the students in the intervention and control groups are similar with regard to the current smoking prevalence (2.4% and 2.7%, respectively), never-smoking prevalence (85.0% and 84.0%, respectively), and the proportion of those having at least one smoking parent (38.6% and 38.4%, respectively).This large study is conducted in five German federal states. Our definitions for the smoking status of the various monitored tobacco products stem from the National Youth Tobacco Survey by the Center for Disease Control (Atlanta, United States) [57]. Teachers are used as data collectors and were handed out a modified protocol, as used in the Hutchinson Smoking Prevention Project to ensure international comparability.

This is also the first national study to show that current e-cigarette prevalence is higher than cigarette smoking prevalence in Grade 7 students from secondary schools (2.6% use cigarettes and 4.7% use e-cigarettes). More than a quarter of these (1.3% of the total sample) currently use both products at the same time. The epidemiologic data presented here are therefore also valuable, considering that the most cited and most recent surveys in Germany were conducted via telephone interviews, a method showing poor consistency with biochemical validation in our age group [17,63]. We are not using biochemical validation in our study because it would have to take place in the school setting with previous notice on the day the paper questionnaires are given out. This would compromise the comparability of data obtained on that day, since students may answer according to social desirability.

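### Cheap improvement: the main 24-month model names no baseline covariates, although strong predictors of smoking uptake were measured before randomisation, so some precision is probably given up

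*Protocol article*

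**What the plan says.** - Outcomes: the primary outcome is the difference between arms in the change in smoking prevalence from baseline to 24 months.
- Analysis: the main analysis is a hierarchical linear model that "will be used to test for between-group differences in within-group changes in smoking behavior over time". Gender, cultural background and social characteristics are given as examples of further covariates, and these belong to secondary analyses. No covariate, stratification factor or school type is named for the main model.
- Trial Design and Randomization: the baseline survey came before randomisation. Schools were stratified by study centre and by baseline smoking prevalence (below 2.65%, or at or above it).
- Discussion, Baseline Characteristics: "Our baseline survey includes the major predictors of adolescent smoking, as described in the literature". Table 1 reports many of them, for example "One of my best friends smokes" and "Never smoked a cigarette (never-smokers), n".
- Sample Size Calculation: the trial was planned "with an alpha of 5% and a test power of 70" per cent.

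**The concern.** At baseline 2.6% of students smoked and 10,842 of 11,127 (97.4%) did not. At the upper planning rates, most 24-month smokers must come from the second group. If 12% smoke at 24 months, baseline smokers can supply at most 2.6 of those 12 points, so at least 9.4/12 = 78% are baseline nonsmokers; at 9% the share is at least 6.4/9 = 71%. (This ignores dropout. At the lowest planning rates it need not hold.) A 30-day smoking indicator gives all baseline nonsmokers the same value. It cannot tell a student who has never tried a cigarette from one who has experimented, uses e-cigarettes or has a smoking best friend.

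What is at stake is precision. Power was set low, and prognostic information already in hand is kept out of the analysis that decides the trial.

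**Working it through.** **1. The plan's own figure.** The sample size "was calculated with a two-sided Chi-square test and multiplied by the correction factor design effect", for "2% vs 5% up to 9% vs 12%, respectively". Inputs: two-sided 5%, power 70%, cluster size 100, ICC 0.033 ("We calculated an intraclass correlation coefficient of 0.033"), dropout 30%.

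- Design effect = 1 + 99 × 0.033 = 4.267.
- Pooled chi-square formula, 2% vs 5%: 463 per arm; 2 × 463 × 4.267 / 0.70 = 5645.
- 9% vs 12%: 1289 per arm; 2 × 1289 × 4.267 / 0.70 = 15,715.

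Both stated totals are reproduced exactly.

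**2. Unadjusted power at the achieved size.** 11,286 students in 144 schools is 78.4 per school; after 30% dropout, about 55. There are 72 schools per arm. For 9% vs 12%, take p = 0.105. As in the plan's own calculation, this treats the comparison as one of 24-month proportions.

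- Variance of a school mean: v = p(1−p)[(1−Rb) × 0.033 + (1−Rw) × 0.967/55], where Rb and Rw are the shares of between-school and within-school variance explained by covariates.
- Rb = Rw = 0: v = 0.0940 × (0.0330 + 0.0176) = 0.00475.
- SE = √(2v/72) = 0.0115, or 1.15 points.
- Power = Φ(0.03/0.0115 − 1.96) = 74%.

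**3. With covariates.** The documents give no Rb or Rw, so these values are assumptions.

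| Rb | Rw | Variance ratio | Power |
|---|---|---|---|
| 0 | 0 | 1.00 | 74% |
| 0 | 5% | 0.98 | 75% |
| 0 | 10% | 0.97 | 76% |
| 10% | 3% | 0.92 | 78% |
| 20% | 5% | 0.85 | 81% |

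The 20%/5% row is worth about 144 × (1/0.852 − 1) = 25 more schools. The between-school part is 0.0330/0.0506 = 65% of the variance of a school mean, so the gain depends mainly on covariates that explain differences between schools.

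**4. Do the baseline differences amount to bias?** Table 1, intervention vs control:

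- Lower in the intervention arm: current smoking 2.4 vs 2.7%, ever smoked a cigarette 15.0 vs 16.0% (from never-smokers 85.0 vs 84.0%), best friend smokes 10.6 vs 11.8%, older sibling smokes 11.5 vs 12.0%, e-cigarettes 4.4 vs 5.0%, two or more products 3.3 vs 3.9%.
- Level: smoking parent 38.6 vs 38.4%, intention score 0.45 vs 0.44.
- School type: grammar schools 36/72 vs 32/72, the largest visible difference (standardised difference 0.11).

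Dividing each two-proportion z by the square root of the design effect (ICC 0.033 assumed for every item) gives: best friend −1.06, two or more products −0.91, e-cigarettes −0.80, ever smoked −0.78, current smoking −0.53. Grammar school, compared at school level, gives 0.67. All fit chance, and the items are correlated, so they are not separate signals. The first age-of-first-puff band (20.5 vs 25.0%) looks larger, but it covers only students who reported an age (161/784 vs 203/812). Its cluster-adjusted z is −1.86, and over whole arms it is 161/5732 = 2.8% vs 203/5554 = 3.7%.

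**5. Direction.** If students with a smoking best friend have a 24-month risk 5-30 points higher (assumed), the 1.2-point gap shifts the estimate by 0.06-0.36 points towards the intervention. The 5.6-point school-type gap at an assumed 5-10 points gives 0.28-0.56. These overlap and do not add up. In the other direction, a change score subtracts the whole baseline smoking gap of 0.29 points. If the slope of follow-up on baseline is 0.3-0.8 (assumed), that over-corrects by (1 − slope) × 0.29 = 0.06-0.20 points against the intervention. The net sign is not established.

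**The case against.** An unadjusted main analysis with covariates in secondary models is valid in a randomised trial, and nothing in the article contradicts it. The exact fixed effects may stand in a fuller plan that is not shown. Baseline smoking is already in the outcome, and centre and school prevalence were balanced by stratification. Unadjusted power at the hardest planning scenario is 74%, above the planned 70%, and at 7% vs 10% it is 82%. The gain rests on assumed explained variance, and student-level items that explain nothing between schools add little.

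Most of this stands, and it limits the point to an improvement. It does not remove it, because the article does more than stay silent: it assigns covariates to secondary analyses. Stratified allocation also does not lower the reported standard error unless the factors are in the model.

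A reader might infer from Table 1 that the unadjusted result is biased in favour of the intervention. The documents do not support that. Allocation was random, the differences fit chance, the unadjusted standard error already covers such imbalance, and the change score may push the other way. Nor is it right that the plan ignores every predictor, since baseline smoking and school prevalence are handled in part.

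**Conclusion.** This is a cheap improvement, not an error. The plan probably gives up precision by leaving measured predictors out of the main model. The likely gain is from about 74% power to 78-81% at 9% vs 12%, falling to 75-76% if the covariates explain no between-school variance. This assumes ICC 0.033, 55 analysed students per school in 72 schools per arm, and the stated explained variances, which are assumptions because the documents give none. If baseline smoking in the change outcome already captures part of that variance, the further gain is smaller. The observed imbalances are no evidence of bias and should not drive the choice of covariates.

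**What to change.** Before the 24-month data are opened, state that the main model includes:

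- the stratification factors (study centre and school baseline prevalence stratum);
- individual baseline smoking;
- school type, which is neither a stratification factor nor a named covariate and can explain between-school variance;
- a short list chosen for prognosis, for example ever tried a cigarette, current e-cigarette or waterpipe use, and best friend smokes.

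The covariates must act on the 24-month outcome, either in a model of 24-month smoking given baseline or as covariate-by-time terms. A main effect that is constant over time leaves the contrast in change essentially untouched. Add a simple rule for missing baseline items, such as a missing indicator or mean value, so that no student is dropped. Keep the unadjusted model as a sensitivity analysis.

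The cost is wording and a slightly more complex model; no new data are needed. Item non-response has to be handled: the best-friend item has about 1174/0.112 = 10,482 valid answers out of 11,286, so about 7% are missing.
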